**9.4 Procedures for missing data**

All possible effort will be performed, to reduce missing data. An investigator or study nurse will check the completed CRFs before statistical analysis. Missing data will be identified and if possible entered from the source data of the patient. Remaining missing data will be analyzed according to the Intention-to-treat principle.

**9.5 Analysis procedures for deviations from the statistical analysis plan**

Each deviation from the original statistical analysis plan will be described in the protocol and the final report.

**10 Data entry and data management**

**10.1 Data entry**

The respective investigator and study nurse will perform data collection and psodonymization. Only these persons, the monitor and an auditor will have access to the patient files. Pseudonymization will be performed via center number and a consecutively increasing number. The respective physician is obliged to ensure identification of a particular person at any time via the registry-list. Therefore, he will have a identification log with the full patient names. If patient identification is necessary, due to safety reasons, then all respective persons underlie professional secrecy. The investigator is responsible for the correctness and complete documentation of the study data.

**10.2 Data storage**

Study CRFs and the data of the screened but not included patients will be sored together with the completed study documents (study protocol, ethical approval, BfArM-approval) in a locked cabinet with restricted access in the Department of Anesthesiology for 15 years (prescribed by law).

**10.3 Data management**

**10.3.1 Access to source data**

Investigators are obliged to permit authorized third persons access to the source data, according to the legal requirements for quality and protection of data and protection of the study conduction in this center. This includes monitors, auditors, independent Ethical Committees, and authorities. These persons are sworn to secrecy.

**10.3.2 Monitoring**

The sponsor will provide a monitor, who will check all signed patient informed consents and randomly check the accordance of the original data and the CRFs. The investigator is obliged to permit study specific monitoring and enable direct access to the patient files and the source data. Data will be double entered from the paper CRF into the database by to independent student assistants. The responsible biometrician will check both data files for concordance via a coded algorithm. The monitor will be informed if there is discordance between these data files, to check the data in the paper CRF. The investigator will bi inquired for all missing and implausible data, which he has to remove or explain. The student assistants will perform changes in the SPSS database. Data entry and data corrections have to be signed with the name of the respective person, date and time. Monitor will also check intervention performance.

**10.4 Final report**

The principle investigator will create and provide to the sponsor a final report after study data analysis, according to the ICH-GCP guidelines.

**11 Quality control and quality assurance**

**11.1 Quality control**

This study will be conducted in accordance with the ICH Guideline for Good Clinical Practice (GCP) E6, June 1996; the CPMP/ICH/135/95, September 1997; and the legal regulations, to assure a correct, valid and consistent data collection and to guarantee the usage of standardized operating procedures (SOPs).

**11.2 Quality assurance**

The following defaults will be used for quality control:

- Feedback meetings and exercises, for preparation of the investigators for the study SOPs.
- Monitoring of included patients according to the safety criteria.
- The sponsor may visit the study site at any time and inspect the study progress, study conduction, the original data and the CRFs.
- Matching of the original source data and the CRFs.
- Double entry of the paper CRF data by two to independent student assistants into the SPSS database. Verification of these entries by the responsible biostatistician via a coded algorithm.

**12 Ethical and administrative aspects**

**12.1 Explanation of the planned examinations on humans or human material or animals**

This pilot-study is a clinical investigation of an approved drug. All planned investigations in this pilot-study will be conducted in accordance with the medicine law (current version of 2011) and the GCP guideline (current version 2006) based on the Helsinki declaration. This implies an ethical approval, the approval of the competent authority and the non-public registration at the European Medicines Agency (EMEA). We will register this study in a public registry at clinical trials.gov in addition. Patients will be verbally and written informed about the aims, the conduction and the benefit of this study including the personnel benefit and risk. It has to be noted in written form, before enrolment into the study, that inclusion into the study was voluntary and after information and weighing. The patient is allowed to withdraw from study without reasons at any time. Randomization ensures the same chance to be allocated to one of the two groups. Pseudonymization of the patients and their data with a study number preserves data protection toward persons, who are not allowed to see these data (biometrician, data manager etc.). Patient selection and treatment are described under 4 and 5. Surgery and anesthesia are conducted according to the clinical standards and guidelines. A SOP, where only the drug is different will be established for the study anesthesia in both groups (Xe and control). Patients will be closely monitored during anesthesia conduction; safety data like anesthesia data and vital data will be assessed in short intervals as described above. Highest priority has the well being of the patients. If a threatening or occurred damage for the patient appears at any time-point of the study conduction, independently of a causal relationship or not, the study participation will be terminated and an adequate diagnosis and therapy will be induced immediately. All patients will receive a physical examination at the study end (planned/ individual) and will receive further diagnosis and therapy if the result was conspicuous. Summarizing, the investigational product Xe is a safe for anesthesia already approved drug. The risk for study participation does not exceed the risk for general anesthesia for PN. The renal tumor resection tissue will undergo histopathological examination in paraffin sections and a graduation of the tumor stage according to the clinical routine. In addition, there will be produced additional paraffin sections, which will probably be used in this pilot-study for HIF-1α determination in the healthy surrounding tissue by immunohistochemistry. An additional storage exceeding the clinical routine is not planned.

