**2.3 Secondary objectives/ secondary endpoints**

The following data will be assessed as secondary endpoints: Duration of direct manipulation-/ ischemia time during renal tumor resection; duration of anesthetic exposition before and after tumor resection; intraoperative blood loss, tumor size and histology; optional assessment of HIF 1 activation in healthy surrounding tissue; GFR time-course, determined by cystatin C assessment in serum; creatinine time-course within the first 7 days after PN; optional assessment of KIM-1 or NGAL in urine before and after tumor resection; urine output during surgery and on postoperative day 1-3; acute kidney injury with increasing AKIN-classification is already within 48h associated with increased mortality. This association was verified in several studies. A recent meta-analysis showed a doubled risk for mortality (RR= 2.4) for patients with AKIN I compared to patients without. Furthermore, it is increasing continuously from AKIN II to AKIN III (RR = 4.2 and RR = 6.4, respectively) and further on [35].

Macrophage migration-inhibiting factor (MIF) in serum will be assessed preoperatively, 5 minutes after termination of the tumor ground-treatment, directly postoperative in the PACU and after 24h. Additionally we will assess demographic data like age, height, BMI and anesthesia-related data (anesthetic-concentrations and amount of opioids and inspiratory oxygen-concentration) in this pilot-study. These data will be used to check the comparability of the two groups. According to GCP, safety data like vital patient data (oxygen saturation, blood pressure, heart rate) during anesthesia, laboratory data (blood cell count, coagulation data, urea, transaminases, creatine kinase) after surgery and all adverse events (AEs) und serious adverse events (SAEs) will be assessed in addition. After 3-6 months creatinine in serum and GFR should be determined for longer-term renal function course. This will be achieved by contacting of the familiar physician or urologist during the routine post-surgical care.

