**4.4 Patient exclusion criteria and procedure**

**4.4.1 Reasons for premature study-exclusion and termination of the investigational product administration**

- Patient safety has the first priority. A patient will be excluded before intervention, if an exclusion criterion appears after patient inclusion- but before intervention- (e.g. change of the surgical technique, acute patient deterioration, etc.). Patient data will receive a screening number and will be stored in a locker.
- A retrospectively noticed deviation from the inclusion or exclusion criteria (after the beginning of the intervention) will induce a study drop out. Depending on the time-point, the patient will receive a standard anesthesia and the data management will excluded the patient.
- Consent withdrawal: Patients can withdraw whenever they want. All collected data until the withdrawal time-point as well as the randomization group have to be filed. The patient has to be informed, that already collected data will be used further on.
- Severe adverse events (SAE) and suspected severe adverse reactions (SUSAR), which prohibit further study conduction.
- Adverse events (AE) and adverse reactions (AR), which seem to be hazardous for the physical and psychological health of the patients, as evaluated by the principle investigator.
- Technical difficulties and required modifications of the investigational product administration device.

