**4.4.2 Time-point of patient drop out/ cessation of study treatment**

Each patient may be excluded from this study at any time. If any of the above mentioned condition occurs, the patient will be immediately excluded. If this occurs during the administration of the study-treatment, this will be terminated and replaced by a standard anesthetic. The patient will be treated according to his medical need.

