**7.2 Outcome measures**

Investigator I will assess inclusion criteria and demographic data during visit 0. Intraoperative data will be assessed, documented and analyzed by investigator II during visit 1. Blinded investigator I will assess the remaining secondary outcomes postoperatively until the 7th postoperative day or discharge day (if earlier), respectively. We will maintain two case report forms (CRFs) with all patient data, to assure blinding procedure. One CRF will include visit 0, 2-10, the other one for visit 1. All data outside of range will be validated by the investigator and marked as clinically significant (cs) or not clinically significant (ncs). Each clinically significant value will be considered as an AE and documented in the adverse event section.

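### Section 12.1 ends participation for harm more broadly than 4.4.1, and no section separates stopping the study gas from ending the day 1 to 7 GFR sampling that the primary endpoint needs

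*Protocol*

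**What the plan says.** Protocol section 12.1 states the trigger as "If a threatening or occurred damage for the patient appears at any time-point of the study conduction, independently of a causal relationship or not", and the consequence as "the study participation will be terminated and an adequate diagnosis and therapy will be induced immediately". The words where the two meet, "independently of a causal relationship or not, the study participation will be terminated", show that what ends is participation, not only the anesthetic.

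Section 4.4.1 is narrower. Among adverse events and reactions it lists only those "which seem to be hazardous for the physical and psychological health of the patients, as evaluated by the principle investigator", and among serious events only those that rule out continuing the study. Its heading covers exclusion from the study and termination of the study drug together. Section 4.4.2 adds: "If any of the above mentioned condition occurs, the patient will be immediately excluded". Section 4.4.3 keeps the data up to exclusion.

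On laboratory results, section 7.2 says: "Each clinically significant value will be considered as an AE and documented in the adverse event section". Section 8.3 repeats this, and section 8.2.2 lists creatinine and cystatin C among the variables in every sample. No section exempts them.

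The primary endpoint (2.2, 7.1.2) is baseline GFR minus the lowest GFR on postoperative days 1 to 7. The intervention lasts around 3 hours (4.1).

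**The concern.** The study drug is finished before the first postoperative GFR is taken. Ending participation after surgery therefore stops no study treatment; it stops only measurement. If renal decline can itself be taken as the harm that ends participation, whether a day's GFR is missing depends on the GFR already seen.

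The value that prompts exclusion is kept. What is lost is any later, lower value, so the recorded maximum decrease may be too small. With the same rule applied in both arms, this happens more often in the arm with the deeper falls. If xenon works, that is the control arm, and the measured benefit shrinks. For a pilot whose result decides whether a larger trial follows, that is the unwelcome direction.

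**Working it through.** The protocol gives no figure on this point, so the main check compares the sections.

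**Step 1: are the two rules the same?** Section 4.4.1 has two filters: the principal investigator's judgement that an event is hazardous, and for serious events that they rule out continuing. Section 12.1 has neither, and it adds damage that is merely threatened. One patient could stay in under 4.4.1 and be terminated under 12.1.

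**Step 2: does exclusion reach the sampling period?** Yes. Section 12.1 applies at any time-point. Section 4.4.2 treats events during administration of the study drug as a special case, so later exclusion is foreseen.

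**Step 3: does another section restore the data?** Section 4.4.3 stops at exclusion. Section 4.4.5 recommends a final examination to patients who withdraw, not daily sampling. Section 8.4 provides for continued observation after an adverse event, but as clinical care; it is not said to supply study GFR values.

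**Step 4: can renal decline be the trigger?** Sections 7.2, 8.2.2 and 8.3 make a clinically significant creatinine or cystatin C value an adverse event. Section 2.3 ties AKIN stage I to a mortality risk ratio of 2.4. A site could reasonably see such a patient as harmed. Against this, sections 5.3 and 7.1.3 schedule the AKIN assessment on days 1 and 2 and creatinine to day 7 or discharge, which assumes that these patients stay in.

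**Step 5: size, as an illustration.** Inputs from 9.1: mean maximum decrease 54 (control) and 36 (xenon) ml/min/1.73 m², with the 30 there read as the SD. This gives (54 − 36)/30 = 0.6, the standardized difference that 9.1 also uses. Assumptions of mine: patient decreases normal, floored at 0; nadir day uniform on days 1 to 4; linear fall to the nadir, then recovery by 10% of the nadir fall per day; daily noise SD 5; 200,000 patients per arm. The series ends on the first day the fall reaches the trigger, and nothing is imputed. Share lost = (full difference − truncated difference)/full difference.

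| Trigger (ml/min/1.73 m²) | Cut before day 7, control / xenon | Full difference | Truncated difference | Share lost |
|---|---|---|---|---|
| 30 | 81% / 61% | 15.7 | 8.9 | 6.8/15.7 = 43% |
| 45 | 63% / 40% | 15.9 | 11.8 | 4.1/15.9 = 26% |
| 60 | 43% / 22% | 15.7 | 14.0 | 1.7/15.7 = 11% |
| 75 | 25% / 10% | 15.9 | 15.4 | 0.5/15.9 = 3% |
| 90 | 12% / 4% | 15.8 | 15.6 | 0.2/15.8 = 1% |

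The full difference is below 18 because of the floor at 0 and because the maximum of noisy days adds more to small falls.

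On the percentage scale (30% against 20%; SD 10/0.8 = 12.5 to 10/0.6 = 16.7 points; noise SD 4), several trajectory shapes with a trigger at a 30% fall lose 21 to 33% when the nadir is on day 3 or 4, and 6 to 9% when it is on day 1 or 2. With the trigger set so that about 9% of all series are cut, close to the 10% dropout expected in 9.1, the loss is about 2% (nadir day 3 or 4) or 1% (day 1 or 2).

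**The case against.** The strongest reply is that no section says a fall in GFR ends participation. Section 12.1 speaks of damage, not of adverse events. A laboratory value becomes an adverse event only if the investigator marks it clinically significant, and the stated consequence is documentation and informing the sponsor. A 30% mean fall is the expected course in controls, and the AKI outcome needs these patients to be followed. Section 12.1 also refers to sections 4 and 5 for patient selection and treatment, so 4.4.1 may be meant to govern. All of this stands. A reader might infer that the protocol orders termination on the day AKI is found; it does not. It leaves that reading open.

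A reader might also take the disregard of causality as what makes 12.1 wider. The adverse event definition in 8.4 does not require causality either, so the adverse event trigger in 4.4.1 is not limited by cause. The difference lies in the missing filters.

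The third reply is that 9.2 keeps all randomized patients and 9.3 imputes missing values under a statistical analysis plan. This softens the consequence, and the simulations ignore it. But imputation cannot recover a later, lower value that was never measured, and here the gap would depend on the outcome.

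**Conclusion.** The conflict between 12.1 and 4.4.1 is real, and so is the failure to separate the end of treatment from the end of measurement. That a renal decline can cut its own series is a permitted reading, not a stated rule.

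Any such truncation works toward a smaller difference between arms. Its size cannot be fixed from the protocol, because the trigger, the nadir day and the imputation are not stated there; section 1.1 speaks only of an initial nadir. It runs from about 2% or less, if only very deep falls trigger exclusion, to 21 to 33% with a trigger at a 30% fall and a nadir on day 3 or 4. The upper end is an extreme case and should not be read as the expected loss: it puts the trigger at the mean control fall and would cut over half of the control series, against an expected dropout of 10%. The still lower trigger in the first table row cuts 81% of control series and is less plausible again.

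The point deserves correction because the remedy is cheap and concerns the primary endpoint, not because a large bias has been shown.

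**What to change.** Reconcile 12.1 with 4.4.1 to 4.4.3 so that one termination rule applies throughout. Which clinical stopping rule that is remains for the sponsor to decide.

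In the same sections, distinguish ending study treatment from ending data collection. State that stopping the study treatment, or excluding a patient because of harm, does not end collection of the already scheduled daily creatinine and cystatin C up to day 7 or discharge, unless the patient withdraws consent. The intention-to-treat analysis in 9.2 and 9.3 would then rest on measured rather than imputed nadirs for these patients.

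The cost is protocol wording and continued data entry for a few excluded patients. No additional patients or procedures are needed, since the samples are already in the schedule.

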**12.4 Protocol amendments**

Any modification of the predefined trial conditions in the study protocol is not planned, for assurance of proper data analysis. Any modifications to the study protocol that may impact the conduct of the study are possible in exceptional cases. Modifications will only take place in coordination of the investigator with the sponsor. All modifications of the study procedure have to be made in written form in the study protocol, stating the reasons, and signed by all responsible persons. Each amendment becomes part of the study protocol. Substantial amendments (e.g. change of the drug dose and/ or other significant changes, which may influence the safety of the study participants), have to be approved by the respective Ethics Committee and/ or the respective regular authority, as well as the patients. The amendment has to be provided to the regular authority (BfArM).

**12.5 End of study**

End of study will be reported by the sponsor to the regular authority within 90 days, in accordance with § 12 and 13 GCP-V.

**12.6 Final report**

The sponsor will provide the final report to the regular authority within one year, in accordance with § 13 GCP-V.

**13 Documentation**

**13.1 Data collection and management**

**13.1.1 Source data**

All data from the study related examinations and surveys will directly be documented in the case report forms (CRFs) and considered as source data. Additional information from not-study related examinations, or data from the patient file (like ECG and laboratory data print-outs), respectively, will be copied, considered as source data and filed in the CRFs.

**13.1.2 Case Report Forms (CRF`s)**

Two CRFs will be created for each patient. One for the data of investigator I, one CRF for data collected by investigator II. CRFs will be filled in manually with a water insoluble pen. CRFs will be stored according to point 10.2. The principle investigator will create a final report, after study data analysis, according to the ICH-GCP guidelines and provide it to the sponsor.

**13.2 Digitalization of study data**

The investigator or study nurse will check the completed CRFs with regard to completeness and correctness. Data will be double entered from the paper CRF into the SPSS database by to independent student assistants, to check the concordance via a coded algorithm. This will be followed by the statistical analysis.

**13.3 Storage of study data**

The sponsor of this study - Clinical Trials Center Aachen (CTC-A), University Hospital Aachen, [name] - is obliged, according to the ICH Topic E6 (R1) Guideline for Good Clinical Practice (CPMP/ICH/135/95), to store all important documents (described in 8.2-8.6) for 15 years. The final report has to be stored for 5 years. Documents from a prematurely terminated study have to be stored for 2 years.

Above-mentioned important documents, will be sored by the principle investigator) in a locked cabinet with restricted access in the Department of Anesthesiology for 15 years (prescribed by law). The principle investigator is obliged to prevent an erroneous or premature destruction of these documents.

**14 Formal regulations**

This study will be performed in concordance with the study protocol, the German medical act (AMG), the ICH-GCP guidelines, Declaration of Helsinki, and the publication of principles for correctly conducted clinical trials with medical products.

**14.1 Funding**

The German Research Foundation (DFG) and the Department of Anesthesiology (University Hospital Aachen, director: Univ.-[name]. [name]) will fund this study. All detailed, financial aspects for this study will be noted in separate agreements.

